#### *Radiation therapist *experience

A questionnaire specific to this study [see Additional file 2] will be completed by treating radiation therapists to assess their experience with breast positioning in both treatment arms regarding factors including ergonomic concerns, workflow, convenience, and perceived drawbacks. For each patient, the survey should be completed by two treating therapists during the last two weeks of treatment.

#### Workflow

Treatment and setup time will be measured weekly until treatment completion.

### Statistics and analysis

#### Sample size calculation and recruitment period

Based on evidence from previous studies [5–8], we expect a control arm rate of 50% for any degree of MD in the IMF. Due to a reduction in skin folds and reduction in V105% with reduced breast separation, we hypothesize a rate of 30% moist desquamation in the study arm (i.e., an absolute decrease in incidence of 20%). For this effect size with 80% power and two-tailed α = 0.05, the sample size is 93 patients in each arm. Because of the nature of the study and 10% observed loss to follow-up in our pilot study, we will enroll 110 patients in each arm.

We expect that a 3-year recruitment period will be sufficient for the trial. A similar multicentre study from our team [5] achieved a similar recruitment rate in the same patient population drawing from only two centres.

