## Background

The majority of patients with in-situ and early-stage breast cancer receive adjuvant breast radiation therapy (RT) after breast conserving surgery, with adjuvant RT reducing the relative risk of cancer recurrence by half to two thirds [1] while offering minimal overall toxicity, good cosmetic results, and improved quality of life [2].

Some breast RT patients experience skin toxicity [3], which may include moist desquamation (MD), a painful breakdown of skin that can impact quality of life [4]. Development of MD has been found to depend on multiple factors, including the skin dose, the presence of skin folds, breast size, breast ptosis, and body mass index (BMI). Several studies of supine breast RT using varying fractionation schedules, use of beam-modifying wedges or intensity-modulated radiation therapy (IMRT), all concur that the group expected to be at highest risk of MD consists of patients having prominent infra-mammary fold (IMF) areas, BMI greater than 30, brassiere cup size D or larger, and large mid-breast separation [5–8].

Various approaches to supine breast positioning for patients with large or pendulous breasts have been investigated [9]. Currently, there is no accepted standard for supine breast positioning supported by peer-reviewed evidence for large or pendulous breasts. Brassiere use in supine breast RT was reported to reduce lung and heart volume for left breast patients but resulted in higher rates of acute skin toxicity [10]. Thermoplastic shells have been reported to reduce heart dose for left breast patients who are not eligible for breath hold techniques, but this technique is problematic for very large patients and rate of occurrence and degree of MD has not been reported [11]. Prone positioning has also been investigated as a potential solution to the problem of skin folds for pendulous breasts [12–20]. While some success has been achieved in reducing lung dose and eliminating IMF, the prone technique is generally not suitable for patients requiring nodal irradiation and may increase dose to the heart in some treatment conditions. Moreover, the prone position is not tolerable for all patients. The risk of MD in the infra-mammary area for the large or pendulous breast population is expected to be up to 50% with standard supine positioning, even with IMRT, when the whole breast is treated.

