**Fig. 2 Fig2:**
[figure not shown]
Axial CT images of the patient shown in Fig. 1 without CARA (**a**) and with CARA (**b**). The tangential beams and target volume are shown

Following the phase II study, three significant changes were implemented to reduce the incidence of MD in the context of IMF removal using CARA. First, the CARA cradle was re-designed to remove dose due to scatter arising from the attachment to the supporting bracket, resulting in CARA V2.0. Second, the material system was re-designed to reduce the areal density of the entire carbon-fibre cradle by 50%, further reducing the expected skin dose by approximately 10% across all areas of the breast in contact with the cradle. The current version of the cradle, CARA V3.0, incorporates this modification. In addition, a sliding window IMRT technique has now been introduced for tangential breast irradiation. With the established benefits of removing the IMF and reducing breast separation using CARA, tighter dose constraints on V105% can now be met using the sliding window technique. An IMRT dose constraint of V105% < 2% of the optimization target volume (OTV) is now in use.

To address deficiencies in measuring MD using standard scoring systems [27] and to alleviate the difficulty in having patients return to the clinic multiple times post-RT, patient-reported outcomes (PRO) are now the primary measure. Patient-reported outcomes are recognized as important clinically relevant outcome measures in modern radiation oncology [28–31]. Our institution established and validated the Prospective Outcomes and Support Initiative (POSI) methodology to collect PRO information [32]. A recent study investigated PROs for degree and location of skin reaction, pain, sleep disruption, and activity interruption for patients receiving whole breast RT [33]. The sensitivity and specificity for patient-reported incidence of MD were 87% and 76% respectively using open skin as an indicator of MD. The PRO instrument used in that study is in use in this trial.

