### Study design

This is a phase III multicentre trial with patients randomized to two treatment arms of equal sample size. Arm 1 (experimental arm) patients will receive CARA V3.0, while arm 2 (control arm) patients will be treated according to the current standard of care at the treatment centre (without CARA V3.0). The study schema is shown in Fig. 3.

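### The stated 80% power makes no allowance for the reported error of the patient-reported endpoint; if 50% and 30% are true rates, power at 99 per arm is about 42.5% to 73%

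*Protocol article*

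**What the plan says.** The section on sample size calculation and recruitment period gives the planning rates: "we expect a control arm rate of 50% for any degree of MD in the IMF", based on earlier studies, and "we hypothesize a rate of 30% moist desquamation in the study arm (i.e., an absolute decrease in incidence of 20"%). The 30% is justified by fewer skin folds and a lower breast V105%. The result is: "For this effect size with 80% power and two-tailed α = 0.05, the sample size is 93 patients in each arm". For attrition it adds "10% observed loss to follow-up in our pilot study, we will enroll 110 patients in each arm". Allocation is equal (Study design: "patients randomized to two treatment arms of equal sample size").

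The Background, in the text after Figure 2, makes patient-reported outcomes the primary measure and reports their accuracy from a separate study: "The sensitivity and specificity for patient-reported incidence of MD were 87% and 76% respectively using open skin as an indicator of MD". It continues: "The PRO instrument used in that study is in use in this trial".

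The primary endpoint section counts MD as present when the patient reports open skin in the past week and locates it under the breast, unless a trained, blinded assessor has definitively excluded it. It has no corresponding rule for adding MD that the patient did not report. Under Staff skin assessments and Table 1, the staff check is required in the last week of treatment (the last day for five-fraction schedules). After that it depends on the patient's preference.

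**The concern.** The article reports how often its instrument misclassifies MD and then sizes the trial as if it never did. Misclassification that is equal in both arms pulls the observed rates together. A true 20-point difference therefore appears as a smaller one, and the trial has less power to detect it than the article states. This matters most if the result is not significant. A reader who takes 80% at face value would treat that as fairly strong evidence against a 20-point benefit, when the endpoint may have given much less chance of showing one.

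**Working it through.** **Inputs.** True rates 50% and 30%, two-sided α = 0.05, 80% power, 10% loss, 110 enrolled per arm (sample size section); sensitivity (Se) 0.87 and specificity (Sp) 0.76 (Background). Evaluable per arm: 110 × 0.90 = 99.

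**Step 1: reproduce the plan.** With p̄ the mean of the two rates,

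n = [1.96·√(2p̄(1−p̄)) + 0.8416·√(p₁(1−p₁) + p₂(1−p₂))]² / (p₁−p₂)².

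For 0.50 and 0.30, p̄ = 0.40 and the roots are √0.48 = 0.6928 and √0.46 = 0.6782. So n = (1.3579 + 0.5708)² / 0.04 = 93.0. The stated 93 is reproduced. Allowing for loss, 93/0.90 = 103.3, so 104 per arm would suffice, and 110 covers it.

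**Step 2: power without measurement error at 99 per arm.**

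Power = Φ{[(p₁−p₂)√n − 1.96·√(2p̄(1−p̄))] / √(p₁(1−p₁) + p₂(1−p₂))}.

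(0.20 × 9.950 − 1.3579)/0.6782 = 0.932, which gives 82.4%.

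**Step 3: observed rates under misclassification.** Observed rate = p·Se + (1−p)(1−Sp). The difference shrinks by the factor Se + Sp − 1. Staff exclusion of false positives raises Sp. Under the stated rule it leaves Se at 0.87.

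- No false positives removed (Sp 0.76): 0.435 + 0.120 = 55.5% and 0.261 + 0.168 = 42.9%. Difference 20 × 0.63 = 12.6 points.
- Half removed (Sp 0.88): 0.435 + 0.060 = 49.5% and 0.261 + 0.084 = 34.5%. Difference 20 × 0.75 = 15.0 points.
- All removed (Sp 1.00): 43.5% and 26.1%. Difference 20 × 0.87 = 17.4 points.

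**Step 4: power on those rates, with the formulas above.**

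| False positives removed by staff | Observed rates | Power at 99 per arm | Evaluable per arm for 80% |
|---|---|---|---|
| None | 55.5% vs 42.9% | 42.5% | 246 |
| Half | 49.5% vs 34.5% | 57.2% | 169 |
| All | 43.5% vs 26.1% | 73.3% | 117 |

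Worked line for the last row: (0.174 × 9.950 − 1.96 × 0.6736)/0.6623 = 0.62, and Φ(0.62) = 0.73. With perfect exclusion and no loss at all (110 per arm), power is 78%, still short of 80%.

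**Step 5: the other reading.** If 50% and 30% are already rates on the trial's endpoint, the stated power holds. The true difference must then be larger than 20 points: 20/0.87 = 23.0 with perfect exclusion, and 20/0.63 = 31.7 with none.

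**The case against.** The strongest reply is that nothing in the sample size section is miscalculated, and that its 80% is tied to a named effect. That is right: this point concerns the scale of the inputs. The attenuation exists only if 50% and 30% are true rates, and the article does not say so. If they are endpoint rates, no power is lost. The text leans towards true rates. The 50% comes from earlier studies and the accuracy figures from a different, recent one. Patient reporting is presented as a change from the pilot, and the 30% is argued from physical mechanisms. The cited studies are not at hand, so the question stays open.

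A reader might also infer that power is simply 42.5%, or that 246 per arm are needed. The documents do not support this. The 87% and 76% describe open skin alone, whereas the endpoint also requires the location item, and a staff check is mandatory in the last week of treatment. The figure is the no-correction end of a range. Nor does the article say whether the accuracy is per questionnaire or per patient, while the endpoint is collected weekly. Carrying it over is therefore an assumption.

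The Staff skin assessments section settles disagreements between assessors on the primary outcome by majority vote. That could be read as letting staff add unreported MD. If so, sensitivity could exceed 87% and power could move from 73% towards the error-free 82.4%. The endpoint definition itself provides only for exclusion.

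The primary analysis is covariate-adjusted logistic regression, while these figures are unadjusted. The plan's 93 also comes from an unadjusted formula, so like is compared with like.

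Two further inferences fail. The Background's "The risk of MD in the infra-mammary area for the large or pendulous breast population is expected to be up to 50"% might suggest a lower control rate and hence lower power. Under the stated absolute 20-point reduction, power rises instead: 40% versus 20% gives 87.2% at 99 per arm. It falls only if the relative reduction is held: 40% versus 24% gives 67.7%. And although patients with lateral ptosis but no fold are eligible, the documents give neither their share nor their risk, so no loss of power can be derived from them.

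**Conclusion.** The point holds in a conditional form. The 93 per arm is correct for 50% versus 30%, but the stated power ignores the error that the article itself reports for the instrument behind its primary endpoint. At 99 evaluable per arm, power for the unadjusted comparison is about 73% at best under the stated exclusion rule, about 57% if half the false positives are removed, and 42.5% if none are. This rests on three assumptions: 50% and 30% are true MD rates, the error is the same in both arms, and the reported sensitivity and specificity carry over to this endpoint. The second is not guaranteed, since patients know their arm. The documents do not support a single figure within the range, a claim that the sample size is miscalculated, or any loss of power from the control rate or the no-fold patients.

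**What to change.** In the sample size section, state whether 50% and 30% are true MD rates or rates on the endpoint as scored.

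- If true rates: give the sensitivity and specificity assumed after staff review, the observed rates expected in each arm, and the resulting power at 99 per arm (about 42.5% to 73% on the figures above), in place of an unqualified 80%.
- If endpoint rates: say so, justify them on that scale, and give the larger true difference implied (about 23 points with perfect exclusion of false positives, about 32 with none).

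In either case, say whether the majority vote can add MD that the patient did not report, because this determines whether sensitivity is capped at 87%.

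The number of patients need not change. The cost is one rewritten paragraph and, under the first reading, a less favourable stated power.

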#### Randomization procedure and tracking

The random allocation lists will be computer-generated by a statistician not associated with the study. Randomization will use permuted blocks of random size. Stratification is by dose fractionation, by presence of IMF skin fold, and by centre.

The allocations will be uploaded into a password-protected website on secure hospital servers. When an eligible and consenting patient is identified in advance of their CT simulation appointment, the study coordinator or study radiation therapist will enter a patient identification code, and the computer will issue the allocation and a patient study number. An automated audit trail will track the patient identifier and study number, the treatment allocation, and the date, time, and site of the transaction.

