#### CT simulation

CT simulation will be performed with the patient in supine position for both study arms. The preferred patient position is both arms above the head with elbows resting comfortably on a wing board. Variation in arm position (one arm up) is acceptable if the patient is unable to achieve both arms up. Arm position shall be documented on the treatment planning data sheet. Simulation will be performed using the standard CT protocol at the treating centre, confirmed during the credentialing review. Setup marks will be placed laterally and medially, and tattoos will be applied for future setup at the treatment unit. The preferred method for eliminating patient roll at the time of treatment is to place lateral tattoos on each side of the patient with arms up at the time of simulation. Alternate methods will be confirmed at the time of the credentialing review.

Detailed technical descriptions and figures of CARA are published elsewhere and similar to the completed pilot studies [24–26]. In the experimental arm, CARA settings will be adjusted on a patient-by-patient basis to eliminate the IMF and lateral tissue droop such that that all palpable breast tissue sits anterior to the mid-axilla line. Patient-specific CARA settings will be captured to include in the setup instructions at the treatment unit.

Patients in the control arm will be positioned according to standard practice of care which may include no support, a small foam wedge in the skin fold, a thermoplastic shell, or an alternative supine breast support approved at the time of credentialing review. The method will be recorded with the treatment planning data. No changes to standard practice in the control arm, as reported on the credentialing survey, are permitted during this study without consultation with the steering committee.

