### Data collection

#### Baseline assessment

Data collection activities are shown in Table 1. Patients will have a baseline assessment prior to the first treatment. Patient height and weight, BMI, age, smoking status, RT prescription (including boost), adjuvant chemotherapy, brassiere size (band and cup size), IMF skin fold depth in treatment position, and presence of other skin folds will be recorded. The skin will also be assessed at baseline for any pre-existing conditions such as erythema, telangiectasia, desquamation, or infection. At CT simulation, a baseline photograph of the IMF skin will be acquired as well as a photo of the patient in treatment position. A PRO questionnaire is also collected at baseline.

**Table 1 Tab1:** Schedule of activities and data collection

**Study Activity**	**New patient appointment with radiation oncologist**	**Prior to CT simulation**	**Prior to first treatment**	**Weekly during Breast RT**	**Post-RT weekly to 7 weeks from start of breast RT**
Introduction to study	**X**				
Inclusion/exclusion criteria screening	**X**	**X**			
Informed consent obtained		**X**			
Enrollment and randomization		**X**			
Baseline assessment			**X**		
Patient-reported outcome questionnaire			**X**	**X**	**X**
Skin assessment performed by staff			**X**	**Last week of RT, or for five-day fractionation, last day of RT**	**Optional per patient preference**
Skin dose measurement				**Up to three times per patient; optional for sites other than the coordinating site**	
Timing of clinical flow				**X**	
Standard imaging				**X**	
CBCT imaging				**Up to three times per patient**	
Therapist satisfaction				**Last week of RT, or for five-day fractionation, last day of RT**	

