#### *Statistical methods – *primary* outcome*

The proportion of patients experiencing MD in the IMF in the two arms will be compared using logistic regression to assess the effect of treatment, adjusting for brassiere cup size, skin fold size, BMI, smoking status, and dose fractionation schedule. An unadjusted comparison will also be made using the chi-square test, or Fisher’s exact test, if appropriate. Those participants who do not complete all follow-up but have reported MD are included in the analysis. Those who do not complete all follow-up and do not report MD will be excluded from the primary analysis. A sensitivity analysis including those lost to follow-up will be done using multiple imputations for missing data.

Baseline descriptive variables (e.g., age, smoking status, BMI, as described in the section Baseline Assessment) will be compared descriptively between the two arms of the study and assessed for imbalance. Formal statistical comparisons of baseline characteristics in RCTs are not advised [35].

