#### Statistical methods – secondary outcomes

The eight secondary endpoints will be compared between the two study arms as follows:Degree of MD in the IMF: Peak measured area (cm^2^) of patchy MD and confluent MD will be compared where data is available. It is anticipated that a good proportion of patients will have no MD and hence a measured area of zero. Thus, we will divide the outcome into four categories, the first being zero and the other three will be equal sized groups based on their area score. We will then use the linear trend chi-square test to determine whether the groups differ in their distribution of scores.Peak (worst) modified NCI CTCAE scores for radiation dermatitis will be compared using the chi-square test for trend [36].Dose-volume statistics: values for heart, lung, and body will be compared using the Mann–Whitney U test.Dose-area statistics (*in-vivo* dosimetry): Measured skin dose-area statistics will be compared within both study arms. The measured skin dose-area data for patients developing MD in the location where the dose was measured will be compared with that of patients not developing MD in that location to determine if a dose-area metric predictive of MD can be found for either arm.PRO: The peak (worst) PRO breast symptom scores will be compared using a between-groups t-test, or if data do not conform to test assumptions, the non-parametric Mann–Whitney U test. The requirement for steroid cream and analgesics will be compared using the chi-square test, or Fisher’s exact test, if appropriate.Clinical workflow: Time for patient setup will be compared between study arms using a between groups t-test.Reproducibility of patient setup, as assessed by variation in surgical clip positions measured on imaging will be compared between study arms using the F-test.Therapist satisfaction: Therapist satisfaction with the setup procedure as measured by the questionnaires will be compared using a linear trend chi-squared test.

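### Randomization is stratified by centre but the primary logistic model omits centre, which makes the test conservative and costs power if centres differ

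*Protocol article*

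**What the plan says.** Under Randomization procedure and tracking: "Randomization will use permuted blocks of random size". "Stratification is by dose fractionation, by presence of IMF skin fold, and by centre".

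Under Statistical methods – primary outcome, the arms are compared on MD by logistic regression "adjusting for brassiere cup size, skin fold size, BMI, smoking status, and dose fractionation schedule". The abstract gives the same list. So fractionation enters the model directly, the fold factor enters as fold size, and centre does not appear. The supporting analysis has no strata: "An unadjusted comparison will also be made using the chi-square test, or Fisher’s exact test, if appropriate". No reason is given for leaving centre out.

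The protocol lets practice vary by centre. Under CT simulation, control patients are positioned by "standard practice of care which may include no support, a small foam wedge in the skin fold, a thermoplastic shell", or by another approved support. Under Treatment planning and dose constraints, the choice between two IMRT techniques depends on what the centre has.

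For PROs, Statistical methods – secondary outcomes says: "The peak (worst) PRO breast symptom scores will be compared using a between-groups t-test". The Mann–Whitney test is the fallback, and neither uses baseline. Yet under Baseline assessment, "A PRO questionnaire is also collected at baseline". On timing, "Patients will have a baseline assessment prior to the first treatment". Table 1 puts randomization earlier, before CT simulation, and Staff skin assessments states that patients know their arm.

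**The concern.** Stratified blocks balance the arms within centre, so differences between centres add little to the true sampling variation of the treatment estimate. A model without centre does not know this. Its standard error is larger than the estimate's actual spread, and the test rejects too rarely under the null. In a logistic model, leaving out a prognostic factor also pulls the odds ratio towards 1. The trial would bear the work of stratifying by centre without the power that goes with it.

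The protocol gives grounds to expect centre effects. Besides positioning, the Background links the volume receiving 105% or more of the prescribed dose to MD, and links sliding-window IMRT to a tighter limit on that volume.

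The PRO point is separate and smaller. Patients enter after breast surgery, so pain, sleep and activity scores may already differ between patients before radiotherapy. A comparison of peak scores alone leaves that variation in the error term.

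**Working it through.** **1. The plan's own figure.** Inputs from Sample size calculation: 50% against 30%, two-sided α 0.05, power 80%. With pooled variance, n = [1.960·√(2·0.4·0.6) + 0.842·√(0.5·0.5 + 0.3·0.7)]² / 0.2² = (1.358 + 0.571)² / 0.04 ≈ 93 per arm, as stated. Enrolling 110 with 10% loss leaves 110 × 0.9 = 99 per arm, or 198 in all. The sample size is not in question.

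**2. Centre.** Simulation, 4,000 runs per setting: 198 patients, permuted blocks of 2 or 4 within centre × fractionation × fold presence, Wald test from the logistic model with and without centre. Assumed, because the protocol does not give them: 4 or 8 centres; between-centre SD of 0, 0.5 or 1.0 on the logit scale; conditional log odds ratio 0 or −0.95; prognostic fold size, BMI and two-level fractionation. Cup size and smoking were not simulated. For scale, centres one SD either side of a 50% rate lie at about 38% and 62% for SD 0.5, and at 27% and 73% for SD 1.0.

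| SD | Centres | Type I error, without / with centre | Power, without / with centre |
|---|---|---|---|
| 0 | 4 | 0.051 / 0.054 | 86.2% / 86.4% |
| 0 | 8 | 0.048 / 0.052 | 87.6% / 88.3% |
| 0.5 | 4 | 0.047 / 0.055 | 86.0% / 87.4% |
| 0.5 | 8 | 0.045 / 0.057 | 83.4% / 85.6% |
| 1.0 | 4 | 0.033 / 0.054 | 75.5% / 82.0% |
| 1.0 | 8 | 0.031 / 0.048 | 75.3% / 81.8% |

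The Monte Carlo standard error near 0.05 is √(0.05·0.95/4000) = 0.0034. The SD 0.5 type I errors without centre are therefore within noise of 0.05, while those at SD 1.0 are clearly below it. Compare power within rows only. The conditional effect is held fixed, so the marginal effect shrinks as the SD grows, and the lower power levels at SD 1.0 are not all due to omitting centre.

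**3. Mechanism, SD 1.0 and 4 centres.** Under the null without centre, the mean model standard error is 0.299 against an actual spread of 0.275, which is why the test is conservative. Under the alternative, adding centre raises the mean standard error from 0.312 to 0.354 and moves the mean estimate from −0.809 to −1.005. The ratio rises from 0.809/0.312 = 2.59 to 1.005/0.354 = 2.84.

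**4. A smaller simulation** (5 centres, 100 per arm, 1,500 runs) agreed in direction with a smaller gap: 86% against 89% at SD 1.0, and 84% against 85% at SD 0.5.

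**5. PRO.** Adjusting for a baseline with correlation ρ to the peak score multiplies residual variance by 1 − ρ². For an effect with 80% power unadjusted at 99 per arm:

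| ρ (assumed) | Variance factor | Power |
|---|---|---|
| 0.2 | 0.96 | 81.6% |
| 0.3 | 0.91 | 83.6% |
| 0.5 | 0.75 | 89.9% |
| 0.7 | 0.51 | 97.5% |

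The t-test without baseline had simulated type I error of 0.049–0.052 for ρ from 0 to 0.7 (40,000 runs).

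**The case against.** **The size is assumed.** Neither the number of centres nor the spread between them is given, and SD 1.0 is a wide spread. The protocol permits practice to vary and does not show that it does. This stands, and is why the result is a range that includes no loss.

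**Control positioning varies in one arm only.** Much of its effect would be treatment-by-centre heterogeneity, which a centre main effect does not model. This also stands in part, but planning technique applies to both arms.

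**Fold presence.** A reader might infer that two stratification factors are missing. Fold size already carries most of the presence factor, so the point is confined to centre.

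**The change is not free.** At the planned rates there are 99 × 0.5 + 99 × 0.3 ≈ 79 events. Six fractionation schedules are listed. If coded separately they take 5 terms; with treatment, fold size, BMI, smoking and cup size at one term each, that makes 10. Eight centres as fixed effects add 7, leaving about 79/17 = 4.6 events per term. The simulated model was leaner. This argues for pooling or a random intercept, and against stratifying the supporting test by all three factors at once.

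**Analysis plan.** Details may sit in a document not shown. For the primary model this carries little weight, because the protocol gives an explicit list without centre. For PRO covariates it carries more.

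**Timing of the baseline PRO.** It follows open-label randomization, so knowledge of the arm could have shifted it. This stands as a condition on the adjustment.

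**Conclusion.** The point holds as a moderate matter of efficiency and consistency. The primary model omits a factor used to stratify randomization. If centre is prognostic, the test is conservative: about 1–2 points of power at SD 0.5, 6–7 at SD 1.0 (3 in the smaller simulation), and nothing material at SD 0. All of these rest on assumed centre numbers and spread.

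Three stronger readings are not supported:

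- **That a positive result would be unsafe.** The error is in the conservative direction.
- **That both analyses have miscalibrated error rates.** Baseline PRO is not a stratification factor, so omitting it leaves the t-test at 5% and costs only precision. That test could be slightly conservative for a different reason, that it ignores the strata: 0.044 or 0.039 if they explain 5% or 10% of the variance.
- **That adding centre buys free precision.** In the logistic model the standard error rises. The gain is in power, and the estimate becomes a different, centre-conditional odds ratio.

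The PRO gain depends on a correlation that the protocol does not give and is small at 0.3 or below.

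**What to change.** 1. Add centre to the primary logistic model, with small centres pooled by a rule fixed before unblinding, or as a random intercept. State that the treatment odds ratio is then conditional on centre. Fold size may stay as the carrier of the fold factor.
2. Keep the supporting chi-square or Fisher test as it is, or stratify it by centre only. Stratifying by centre × fractionation × fold would leave sparse cells.
3. Optionally, for PRO items with a meaningful baseline (pain, sleep, activity, but not comfort during treatment), compare peak scores by ANCOVA or proportional-odds regression on the baseline score. State the assumption that knowing the arm did not shift the baseline, and keep the unadjusted comparison as a sensitivity analysis.

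The cost is analysis wording. The allocation system already logs the site and the baseline PRO is already scheduled, so no new data are needed. The price in the model is extra terms set against about 79 events, which pooling or a random intercept limits.
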